#### Sensitivity analysis

To manage the inherent uncertainty in model parameters, we will conduct a range of sensitivity analyses. We will identify cases where small input changes—particularly those related to the improved intervention targeting—produce large variations in the outcome (HIV cases averted). Such cases suggest the presence of a critical variable that merits increased attention. Each parameter in the model will be varied systematically across a range in a series of one-way sensitivity analyses. Those that exhibit the largest magnitude of influence will be varied together in multi-way sensitivity analyses. We plan to visualize findings with a “tornado diagram.”

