**Methods:**

We will conduct a three-phase, sequential implementation study. In Aim 1, we will use the Rhode Island All-Payer Claims Database and State Emergency Department Database data to identify healthcare engagement patterns and gaps in HIV prevention service delivery among people with OUD, including rates of HIV screening, PrEP use, and medications for OUD uptake, across settings from 2012 to 2022. In Aim 2, we will convene a series of five stakeholder-engaged evidence-based quality improvement panels—including with providers, policymakers, and people with lived experience—to co-develop implementation strategies tailored to each care setting (i.e., primary care, mental health clinics, emergency department, and opioid use treatment centers). Finally, in Aim 3, we will develop an agent-based model (ABM) to simulate the population-level effect of implementation strategies developed for each care setting (as identified in Aim 2). The ABM will project outcomes such as HIV incidence, cases averted, and number needed to treat (NNT) over 5- and 10-year horizons under various scenarios. Model parameters will be based on literature and findings from Aim 1. Outputs from the ABM will be used to prioritize feasible, high-impact strategies for future real-world implementation.

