#### Output: implementation strategy package

Implementation strategies are defined as methods or techniques used to facilitate the adoption, implementation, and sustainability of a clinical program or practice, including provider training and decision support, intervention-specific tool kits, checklists, formal practice protocols and guidelines, and economic, fiscal, and regulatory strategies [51, 53]. For each selected implementation strategy, we will define and operationalize each implementation strategy needed to address multilevel barriers by describing the actors, action, targets of the action, temporality, doses, and implementation outcomes [53]. An example of implementation strategy is shown in Fig. 3. We anticipate finalizing up to three care-setting-specific strategy scenarios for simulation testing in Aim 3.

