#### Outcome definition

The base model will represent the status quo—current levels of HIV prevention service delivery across different care settings, as established through Aim 1. Using Python™, we will evaluate the effect of each proposed implementation strategy (developed in Aim 2) on multiple outcome measures over 5- and 10-year projections.

Key outcomes will include projected HIV incidence across the population, as well as the number of new HIV cases averted or caused relative to the base model. We will also assess changes in healthcare utilization patterns and quantify uptake of PrEP and MOUD by setting. For each intervention scenario, we will calculate the number needed to treat (NNT)—defined as the number of HIV prevention service encounters or MOUD prescriptions required to prevent a single HIV infection over a specified time horizon. And lastly, the model will assess the population-level impact of integrating HIV prevention services into OUD care. These outcomes will guide the selection of the most effective and feasible strategy package for real-world implementation and inform the prioritization of approaches for future pilot testing and scale-up.

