### Strengths: Sequential design, real-world data, multi-method approach

This study offers multiple strengths that enhance its scientific and translational value. First, it leverages comprehensive, statewide claims and emergency department data to generate a robust understanding of healthcare engagement among a high-priority, often underrepresented population. Second, the integration of stakeholder-driven input through EBQI ensures that proposed implementation strategies are contextually relevant and grounded in real-world practice. Third, the use of agent-based modeling adds a powerful simulation layer to forecast the long-term impact of competing strategies. Together, these components provide a rigorous, multi-method framework with strong potential to guide scalable and sustainable implementation in diverse care settings.

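### Aim 3's sensitivity analysis ranks parameters by how far they move HIV cases averted, and states no check of whether the leading strategy changes

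*Protocol article*

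**What the plan says.** The Sensitivity analysis section of the protocol article fixes three things.

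- **Coverage.** "Each parameter in the model will be varied systematically across a range in a series of one-way sensitivity analyses".
- **What counts as critical.** An input is singled out if small changes in it "produce large variations in the outcome (HIV cases averted"). The same sentence gives particular attention to inputs tied to intervention targeting. No other output is named.
- **Entry to the multi-way step.** "Those that exhibit the largest magnitude of influence will be varied together in multi-way sensitivity analyses". A tornado diagram is planned as the display.

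The Outcome definition section sets the comparator: "the number of new HIV cases averted or caused relative to the base model". It adds an NNT for each scenario and states the use of the results: "These outcomes will guide the selection of the most effective and feasible strategy package for real-world implementation". The abstract says the same: "Outputs from the ABM will be used to prioritize feasible, high-impact strategies for future real-world implementation". The section on the strategy package gives the number of candidates: "We anticipate finalizing up to three care-setting-specific strategy scenarios for simulation testing in Aim 3". The Strengths section describes the model as a means to "forecast the long-term impact of competing strategies".

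**The concern.** The model is there to support a choice, but the sensitivity analysis is built around a different quantity. Each strategy's cases averted is a contrast with the status quo. How far that contrast moves shows how uncertain the benefit is; it does not show whether one strategy stays ahead of another.

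If two strategies are close, an input that acts mainly on one of them can reverse their order with only a modest effect on its own cases averted. Under the stated rule such an input may be neither flagged nor varied jointly with others. An input acting on all strategies may be promoted although the order does not depend on it. The section on calibration and validation does not fill the gap: its stress test of three rule sets concerns the robustness of outcomes and says nothing of ranking.

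At stake is whether the strategy put forward for real-world implementation is reported with a fair account of how firmly it leads.

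**Working it through.** The article gives no parameter ranges and no results here, so there is no figure to reproduce. The mechanism can be checked with a toy model. **Every input below is an assumption and none comes from the article.**

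Model: cases averted by strategy s = N × e × r_s, where N is baseline infections, e is effectiveness common to all strategies, and r_s is the reach of strategy s.

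Base values: N = 100, e = 0.5, r_A = 0.40, r_B = 0.36, r_C = 0.25.

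Base results: A = 100 × 0.5 × 0.40 = 20.0; B = 100 × 0.5 × 0.36 = 18.0; C = 100 × 0.5 × 0.25 = 12.5. A leads B by 2.0.

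**Step 1. One-way variation, unequal ranges.**

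| Parameter | Range | Largest swing in any strategy's cases averted | A minus B, low to high | Leader |
|---|---|---|---|---|
| N | 50 to 150 | 20.0 (A: 10.0 to 30.0) | 1.0 to 3.0 | A throughout |
| e | 0.3 to 0.7 | 16.0 (A: 12.0 to 28.0) | 1.2 to 2.8 | A throughout |
| r_A | 0.34 to 0.46 | 6.0 (A: 17.0 to 23.0) | −1.0 to 5.0 | B at the low end |
| r_B | 0.30 to 0.42 | 6.0 (B: 15.0 to 21.0) | 5.0 to −1.0 | B at the high end |
| r_C | 0.20 to 0.30 | 5.0 (C: 10.0 to 15.0) | 2.0 | A throughout |

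The two longest bars leave the leader unchanged; two shorter ones displace it. A falls behind B once r_A drops below 0.36, a fall of (0.40 − 0.36) / 0.40 = 10%. Varying r_B does not move A at all, so a tornado diagram drawn for A alone would show no bar for it.

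**Step 2. Equal relative ranges.** The bar order in step 1 owes much to the wider ranges given to N (±50%) and e (±40%) than to r_A (±15%). With N also at ±15% (85 to 115):

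- A runs from 85 × 0.5 × 0.40 = 17.0 to 115 × 0.5 × 0.40 = 23.0, a swing of 6.0, the same as for r_A.
- A minus B runs from 85 × 0.5 × 0.04 = 1.7 to 115 × 0.5 × 0.04 = 2.3, so A still leads.

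The bars are now equal, yet r_A changes the choice and N does not. Swing in cases averted cannot separate them; the between-strategy difference can.

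**Step 3. Dependence on the gap.** Take half-ranges d = 0.03, 0.06 and 0.10 for r_A, with swing in A = 100 × 0.5 × 2d = 3.0, 6.0 and 10.0.

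| r_A minus r_B | Half-ranges of r_A that change the leader | Swing in A |
|---|---|---|
| 0.02 | 0.03, 0.06, 0.10 | 3.0, 6.0, 10.0 |
| 0.04 | 0.06, 0.10 | 6.0, 10.0 |
| 0.08 | 0.10 | 10.0 |
| 0.12 | none | none |

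The problem disappears once the gap exceeds the range over which the parameter is varied.

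**The case against.** The case on the other side has real weight.

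- **The ordering of the bars is not established.** A reader might infer that the tornado diagram will put irrelevant parameters first. The article gives no ranges, and step 2 shows that equal relative ranges can give equal bars. Calibration to observed incidence may also narrow the ranges of shared parameters. That inference is not supported.
- **Shared parameters may matter to the choice.** A reader might infer that transmission or partnership inputs scale all strategies alike and so cannot alter the decision. The planned model is a non-linear dynamic network with heterogeneous agents, and the strategies differ by care setting. Such inputs could act unequally and change the order.
- **Intervention inputs are not ignored.** The sensitivity section draws particular attention to those tied to targeting. The test applied to them is still movement in cases averted.
- **Nothing need go unreported.** Every parameter is varied one-way and each strategy is compared with a common base model. If the sweeps cover all scenarios, the difference between two strategies is a subtraction: (A − base) − (B − base). A reader might infer that a fragile lead would be concealed. The article supports only that no such comparison is stated.
- **Cases averted is not the whole decision.** NNT and feasibility also bear on it, so a difference in cases averted alone would not match it fully either. This argues for adding NNT, not for leaving the criterion as it is.
- **An article condenses.** Ranges and threshold methods can sit in a fuller plan. But the response and the multi-way entry rule are both stated here, and a fuller plan that follows them inherits the mismatch.

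**Conclusion.** The point holds in a limited form. The article fixes a response (movement in cases averted against the status quo) and an entry rule for the multi-way step (largest influence). Neither measures the stability of the choice the model is meant to inform. The rule can therefore leave a decision-changing parameter unflagged and out of the multi-way runs.

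Whether it will do so cannot be told from the article. That depends on the unstated ranges, on how the non-linear model transmits each input to each strategy, and on the gap between strategies. In the toy example, parameters with swings of 3.0 to 10.0 cases changed the leader at reach gaps of 0.02 to 0.08, and none did at 0.12. Those figures show the mechanism; they do not predict this study's results. Because the gap is unknown until the model is run, the check is best specified beforehand.

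**What to change.** Keep the tornado diagram on cases averted, and add the following to the Sensitivity analysis section.

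1. Run each one-way variation for all strategy scenarios, with the same inputs in each.
2. For each parameter, report the difference between the leading strategy and each competitor in cases averted, and in NNT, at 5 and 10 years.
3. Report any value within the parameter's range at which the leading strategy changes.
4. Let every such parameter enter the multi-way analysis, whatever the length of its bar.

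The cost is more output to summarise. If the sweeps were meant for one scenario only, covering up to three means up to about three times the sweep computing, on the cluster already planned. If they were meant for all scenarios, the added work is mainly subtraction and reporting.

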## Discussion

### Importance of a multiphase approach

This protocol outlines a multiphase, multi-method implementation science study to optimize the delivery of HIV prevention services among people with OUD in Rhode Island. By integrating retrospective analysis of big data (Aim 1), stakeholder-driven strategy development (Aim 2), and agent-based modeling simulation (Aim 3), this study aims to generate actionable, context-specific implementation strategies to effectively integrate HIV prevention services—including HIV screening, PrEP, and MOUD—into healthcare settings.

### Anticipated contributions

Our approach addresses critical gaps in the integration of HIV prevention services within systems that serve people with OUD. While the public health urgency of the HIV/OUD syndemic is well-established, real-world implementation of evidence-based interventions among people with OUD remains limited. This study offers several key contributions: (1) a comprehensive analysis of insured (APCD) and uninsured (SEDD) data to identify missed opportunities for HIV prevention; (2) use of an EBQI process to co-design strategies with healthcare providers, policymakers, and individuals with lived experience; and (3) application of ABM to test and predict impact of implementation scenarios. Each aim builds upon one another, producing a validated, context-specific final strategy that is ready for real-world implementation.

### Implementation barriers

Implementation of HIV prevention and MOUD services is influenced by multilevel barriers, including individual-level SDH (e.g., mental health disorders, housing instability, food insecurity, lack of insurance, and financial challenges), and structural level factors (e.g., limited provider capacity, institutional fragmentation, stigma, low PrEP prescribing rate, policy restrictions on PrEP coverage). Moreover, while current PrEP delivery models mainly target men who have sex with men (MSM), they often do not address the needs of people with OUD, who also face barriers in accessing MOUD [27, 56]. To successfully integrate HIV prevention services in diverse care settings, implementation science is needed to overcome these multi-level barriers and design feasible implementation strategies to increase the uptake of both HIV prevention and evidence-based OUD treatments. By engaging stakeholders across the care system from people with OUD experience to policymakers, our EBQI process is designed to develop context-specific solutions that address these barriers. Furthermore, the ABM will allow us to test the feasibility and expected effectiveness of these strategies in silico before piloting them in real-world care settings.

### Strengths: Sequential design, real-world data, multi-method approach

This study offers multiple strengths that enhance its scientific and translational value. First, it leverages comprehensive, statewide claims and emergency department data to generate a robust understanding of healthcare engagement among a high-priority, often underrepresented population. Second, the integration of stakeholder-driven input through EBQI ensures that proposed implementation strategies are contextually relevant and grounded in real-world practice. Third, the use of agent-based modeling adds a powerful simulation layer to forecast the long-term impact of competing strategies. Together, these components provide a rigorous, multi-method framework with strong potential to guide scalable and sustainable implementation in diverse care settings.

### Limitations: Claims data, modeling assumptions, generalizability

There are several limitations of this proposed study. First, claims data may not fully capture behavioral risk factors, patient preferences, or quality of care. Second, the SEDD dataset does not include unique identifiers, limiting longitudinal tracking of uninsured individuals, and we may not capture uninsured OUD patients outside of ED settings, limiting the generalizability of our study. Third, the generalizability of our study findings are further limited by the varied policies on OUD and HIV prevention across different states. However, the methodology could inform similar studies in other states.

### Next Steps

This study represents a pioneering, multidisciplinary big-data approach, integrating mathematical modeling and implementation science to address complex health issues and evaluate implementation strategies. We plan to develop a future R01 project for actual implementation study based on this study, focusing on HIV prevention and MOUD in key settings to maximize impact. Our research, utilizing the APCDs and SEDD data, will have broad relevance, particularly for states heavily impacted by OUD and HIV issues. Importantly, these data-driven insights can guide public health agencies to prioritize limited resources by identifying which healthcare settings, strategies, and populations offer the greatest potential impact for integrated HIV prevention and MOUD delivery.

## Data Availability

The datasets analyzed during the current study, including APCD and SEDD, are not publicly available due to strict data use agreements and access restrictions. Individuals interested in using these data must submit a formal application through the appropriate data custodians. However, the implementation strategies protocol developed in Specific Aim 2, along with the full agent-based models (ABM) and simulation outputs, will be made publicly available to support transparency and future research.

## Abbreviations

ABM: Agent-based model
ABC: Approximate Bayesian computation
APCD: All-Payer Claims Database
CFIR: Consolidated Framework for Implementation Research
CPT: Current Procedural Terminology
EBQI: Evidence-Based Quality Improvement
ED: Emergency department
ERIC: Expert Recommendations for Implementing Change
HCPCS: Healthcare Common Procedure Coding System
HIV: Human immunodeficiency virus
ICD: International Classification of Diseases
MCMC: Markov chain Monte Carlo
MOUD: Medications for opioid use disorder
NDC: National Drug Code
NNT: Number needed to treat
OUD: Opioid use disorder
PrEP: Pre-exposure prophylaxis
RI: Rhode Island
SDH: Social determinants of health
SEDD: State Emergency Department Database
